## Abstract

**Background:**

Digital media and gaming have received considerable interest from researchers and clinicians as a model for learning a broad range of complex tasks and facilitating the transfer of skills to daily life. These emerging rehabilitation technologies have the potential to improve clinical outcomes and patient participation because they are engaging, motivating, and accessible. Our research goal is to develop preventative and therapeutic point-of-care eHealth applications that will lead to equivalent or better long-term health outcomes and health care costs than existing programs. We have produced a novel computer-aided tele-rehabilitation platform that combines computer game-based exercises with tele-monitoring.

**Objective:**

Compare the therapeutic effectiveness of an in-home, game-based rehabilitation program (GRP) to standard care delivered in an outpatient physical therapy clinic on measures of balance, gaze control, dizziness, and health-related quality of life.

**Methods:**

A randomized, controlled, single-blind pilot trial will be conducted. Fifty-six participants with a diagnosis of peripheral vestibular disorder will be randomly assigned to either usual physical therapy (comparator group) or to a game-based intervention (experimental group). Measures to be assessed will include gaze control, dynamic balance, and self-reported measures of dizziness.

**Results:**

The project was funded and enrollment was started in August 2014. To date, 36 participants have been enrolled. There have been 6 drop-outs. It is expected that the study will be completed January 2016 and the first results are expected to be submitted for publication in Spring of 2016.

**Conclusions:**

A successful application of this rehabilitation program would help streamline rehabilitation services, leverage therapist time spent with clients, and permit regular practice times at the client’s convenience.

**Trial Registration:**

Clinicaltrials.gov: NCT02134444; https://clinicaltrials.gov/ct2/show/NCT02134444 (Archived by WebCite at http://www.webcitation.org/6cE18bqqY)

## Introduction

The vestibular sense organs of the inner ear are required to stabilize gaze during head motion and provide an absolute frame of reference with respect to gravity for body orientation and balance. Damage to the vestibular sense organs can lead to a number of symptoms and functional difficulties, including blurred vision, dizziness, disorientation, and falls [1]. The economic impact of vertigo and chronic imbalance is immense. Statistics from 2001 to 2004 estimated that 69 million people in the Unites States aged 40 and older report vertigo and imbalance [2-4].

The recovery of function that patients show following the damage due to peripheral vestibular lesion has long been recognized. Following peripheral vestibular lesions, sensory deprivation studies show minimal recovery [5], whereas targeted activities in enriched environments demonstrate considerable recovery of function [6-9]. A recent meta-analysis [10] demonstrated a moderate to strong evidence that a task-specific approach to vestibular rehabilitation is an effective intervention for unilateral peripheral vestibular dysfunction (PVD).

Improved patient compliance with rehabilitative care plans and increased access to these health services can improve health outcomes for individuals with chronic disabilities. In this regard, recent studies provide descriptions of the benefits of activities facilitated through video gaming. For example, studies have used the Nintendo WiiFit balance board to train and assess balance in elderly patients [11-13]. A similar approach has been developed by [name] and colleagues [14-16] and has extended balance gaming exercises to more demanding surfaces. A recent case study of 3 individuals with PVD by Po-Yin Chen et al [17] involved adapting the Wii mote game controller to track head motion, and to use quick head movements to trigger events in a custom computer game (ie, to initiate a baseball bat to swing and hit a baseball). A preintervention and postintervention cases series was recently conducted by [name] and colleagues [18] in 9 adults diagnosed with PVD who received a home game-based vestibular exercise program. They showed the feasibility and usability of the program. Their findings also demonstrated that using head rotation to interact with computer games, when coupled with demanding balance conditions, resulted in substantial improvements in gaze control, standing balance, and stability of the upper trunk during walking. According to the Dizziness Handicap Inventory (DHI), a self-rating, 25-item questionnaire used to quantify a participant’s perception of dizziness and its impact on quality of life, perception of dizziness decreased significantly. These findings provide preliminary support that a low-cost home game-based exercise program is well-suited to train gaze-control and balance.

## Methods

New telerehabilitation technologies (ie, digital media and innovative computer input devices) may improve clinical outcomes by making rehabilitation more motivating, accessible, and ecological. The research objectives of this study are

1. Compare the therapeutic effectiveness of a home game-based rehabilitation program to standard care delivered in an outpatient physical therapy clinic on measures of balance, gaze control, dizziness, and health-related quality of life; and

2. Examine the time course of change electronic gaze performance measures of participants in the home program.

It is postulated that the home game-based rehabilitation program will result in greater improvement in gaze control, dynamic balance control, and dizziness than a typical outpatient physical therapy regimen.

A randomized, controlled, single-blind pilot trial will be conducted (University of Manitoba Human Research Ethics Board, reference number: H2014:149).

### Recruitment

Recruitment and screening (including diagnostics) will be coordinated by physicians and physical therapists in an outpatient center for vestibular rehabilitation. Based on previous pilot research [18], we expect to be able to recruit 56 participants in 12-16 months. Our power analysis is presented in the following section. The inclusion criteria are (1) age 20-50 years, (2) diagnosis of unilateral peripheral vestibular hypofunction based on a detailed neuro-otological and neuro-orthoptic analysis that includes binocular electrooculography with caloric testing; and (3) possession of a home computer with a Windows or Mac operating system. Exclusion criteria include (1) having a central nervous system disorder (cerebrovascular accidents), multiple sclerosis, epilepsy, migraines), axial injury (fractures of the lower extremities or vertebra, advanced hip/knee osteoarthritis), and limited exercise tolerance.

### Randomization, Allocation Concealment, and Blinding

This study is designed as a randomized controlled pilot trial. Fifty-six participants will be randomly assigned to either a normative physical therapy comparator control group or to the experimental game-based exercise group. Interventions will begin within 1 week of the baseline assessment. The postintervention assessment will be conducted within 1 week of the final intervention session. Assessors will be blinded to the group assignments.

### Interventions

Current treatment for gaze instability due to loss of vestibular ocular reflex consists of rehabilitation techniques that attempt to improve gaze control by enhancing smooth pursuit, saccadic eye movements, and the optokinetic reflex; and by increasing the contribution of the remaining vestibular sensors [19-23]. For this purpose, active goal-directed activities requiring foveation, such as tracking a small visual target or reading aloud and during head movements are essential. The central nervous system must be engaged in purposeful visual fixation and exposed to graded degrees of retinal image slip (ie, head motion and object motion) [24,25]. A number of studies have used virtual reality systems with large screen displays or DVDs for optokinetic stimulation [26-28]. These optokinetic applications can provide a controlled, configurable stimulus to help clients gradually adapt to motion stimuli and visual scenes that typically induce symptoms of dizziness or disorientation. Current treatment for balance impairments includes the use of various support surfaces such as a compliant sponge pad [19,29,30]. This procedure is used to increase the magnitude and frequency of body sway in a graded fashion (analogous to use of a treadmill for gait training).

The control group will receive a standardized vestibular exercise program consisting of the Herdman gaze stabilization exercises [21,22]. This program is presently a standard of vestibular care. Participants will attend an outpatient physical therapy clinic once a week for 8 weeks. The program also includes a 2-minute home exercise program prescribed 5 times per week for a 12-week duration.

The experimental group will receive the game-based rehabilitation program delivered at home. Modern concepts of learning and neuro-adaptation have been incorporated using a task-specific approach [31,32]. This approach is similar to constraint-induced movement therapy [33], and treadmill locomotor training [34] in that it is a means of repetitive task practice and functional, goal-directed, and meaningful activities of graded intensity and complexity. Our approach will include visual fixation tasks accompanied by head and target motion, thus exposing the individual to graded degrees of retinal image slip.

Utilizing an inexpensive, commercial, motion-sensing mouse that interacts with any computer game or application, we have developed a computer-based rehabilitation platform with a therapeutic gaming application [18,35,36]. The motion-sensing mouse is a small, wireless input device with inertial sensors. These sensors and software acquire instantaneous angular position, which is then used to control the position and motion of the on-screen cursor in a manner identical to a standard computer mouse. Velcro secures the motion-sensing mouse to a headband. With this simple method, head motion is required while the participant is searching, tracking, and interacting with visual targets. This approach provides a highly flexible hands-free game-based treatment tool to train gaze control in standing position and while walking, thus incorporating graded balance demands as well as passive head motion. The use of a human interface device-compliant motion-sensing mouse allows a variety of therapeutic exercises to be coupled to a wide range of inexpensive commercial computer games. Though initially designed for clinical use, the easy-to-use and inexpensive motion-sensing mouse allows this intervention approach to be extended to home settings [18]. The use of computer games with a head rotation input device provides a simple method of graded gaze exercises consisting of visual-fixation and ocular-following tasks accompanied by head motion. We have tested and categorized more than 40 easily accessible commercial computer games. Thus, a broad range of exercise and computer game combinations are available to provide a graded rehabilitation program that includes

1. Predictable cyclic target movement with progression to random moving targets.

2. Small-amplitude movements, with progression to large-amplitude movements.

3. Slow movements, with progression to fast movements.

4. Large targets, with progression to small targets, thus requiring increased precision and foveation.

5. Solid or structured backgrounds (ie, minimal to strong optokinetic stimulation).

The amount of head motion can also be graded using a standard optical mouse and then by using the head-mounted motion-sensing mouse.

Six to eight computer games will be selected for each participant from a pool of commercial games purchased from Big Fish Games platform. Examples of computer games that will be used include the following:

1. Aquaball and Action Ball: Horizontal, single-axis brick buster with slow to moderate speed, low to moderate movement precision, a small to moderate number of distracters, and simple to complex 2D backgrounds.

2. Brave Piglet: Vertical, single-axis game play with moderate speed, moderate to high movement precision, a small to moderate number of distracters, and simple to complex backgrounds.

3. Butterfly Escape: Horizontal, single-axis matching colors with low to moderate speed, low to moderate movement precision, a small to moderate number of distracters, and simple and moving backgrounds.

4. Jet Jumper: Horizontal, single-axis driving and jumping game play with moderate to fast speed, moderate to high movement precision a medium number of distracters, and a complex and moving background.

5. Feeding Frenzy: Two-axis game play with slow motion element, low to moderate movement precision, a moderate to large number of distracters, and a moving background.

These computer games require rapid visual search, tracking of multiple objects in all directions, and active head rotations greater than 100 degrees/s. For example, many of the typical game play elements require game sprite movements covering half to full screen and head rotations up to 60 degrees. These movements are often rapid, completed in 300-500 ms. This equates to head velocities over 100 degrees/s, with precision. In general, there are four types of game objects, namely, (1) game sprite, which is controlled by head rotation movements; (2) game target objects with which to interact (sometimes more than one at a time); (3) distractor objects, which must be ignored; and (4) objects that attack the game sprite and require special attention. These game objects can be stationary or move in predictable or complex trajectories. The player needs to foveate and track multiple targets in short periods and produce head rotations to reposition game sprite with respect to game targets while also avoiding distractors or attacking objects. Usually a player’s gaze will be focused on game objects moving in a direction perpendicular or opposite to that of the game sprite or head motion. During these times, vestibular-ocular reflex (VOR) compensation will be required to maintain gaze stability. There will also be times when the eyes and head will be moving in the same direction and this will require VOR cancellation.

Each participant assigned to the experimental group will attend 3 45-minute clinical therapy sessions. Participants will receive training regarding the specific exercises and activities and use of the motion-sensing mouse and computer games. Initially the games will be played in sitting position with a standard optical hand mouse to assess the level of dizziness or nausea. The head motion mouse will be introduced in the first session. To start the exercise program, games will be selected with relatively slow target movements and with stationary backgrounds and few distractors. Game speed/amplitude, precision, number of distractors, and optokinetic features will be progressed as tolerated.

Balance training will be incorporated into the second session by playing the games while standing on a compliant sponge pad. A compliant sponge pad is now a commonly used unstable support surface in balance re-training of clients with peripheral and central nervous system disorders or older adults with a history of falls. A compliant sponge cannot completely reciprocate the normal body forces beneath the feet as the client moves. This increases the magnitude and frequency of body sway, thus increasing balance demands.

Based on the initial 3 clinical therapy sessions, a home program will be prescribed, customized to the participants’ specific balance abilities and tolerance (dizziness). Participants will be instructed to perform their exercise programs 20 minutes per day, 5 days per week. The study’s physical therapist will attend the participant’s home to set up the motion-sensing mouse and computer games, and to assess the area for fall prevention. Each participant will be instructed to use a chair to provide support. The physical therapist will email each participant weekly to monitor progress, inquire about difficulties with the computer equipment, answer questions, and progress the exercises as outlined earlier.

### Recording and Data Analysis

The following information will be collected at baseline prior to start of the interventions: age, gender, work history, history of disease/injury process, and current medications. The assessor will be blinded to participant assignments. The primary outcome measures of the study include measurement of dynamic visual acuity, balance performance, and DHI. The secondary outcome measures of the study include gaze performance and gait analysis.

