The pilot data showed a standardized effect size of .80. Assuming the number of model covariates to be 3, the proportion of variance explained by these covariates to be 10%, and a two-tailed test of the null hypothesis of no group difference at alpha=.05, we calculated that a sample size of 46 is required. Given an expected attrition rate of 20% over the study observation period for objective 2, we propose to recruit a total of 56 individuals to participate, with equal numbers for the treatment and control groups.

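### Three co-equal primary outcomes, but the sample size and the .05 level are set for a single test

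*Protocol article*

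**What the plan says.** In the protocol article, Recording and Data Analysis states: "The primary outcome measures of the study include measurement of dynamic visual acuity, balance performance, and DHI". No order or weight is given to the three. Gaze performance and gait analysis are secondary.

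Statistical Analysis and Power Assessment compares the groups on continuous, normally distributed outcomes by analysis of covariance. It switches to a robust version if there are extreme observations, and to Poisson regression for counts. It gives no adjustment across outcomes and no rule for overall success.

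The power paragraph of the same section describes one test:

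- "The pilot data showed a standardized effect size of .80" (the outcome is not named)
- "Assuming the number of model covariates to be 3, the proportion of variance explained by these covariates to be 10" per cent
- "a two-tailed test of the null hypothesis of no group difference at alpha=.05"
- "we calculated that a sample size of 46 is required"
- "we propose to recruit a total of 56 individuals to participate, with equal numbers for the treatment and control groups"

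No power level is stated. The Methods section postulates that the home programme "will result in greater improvement in gaze control, dynamic balance control, and dizziness than a typical outpatient physical therapy regimen".

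**The concern.** Three unranked primaries give three chances to find a group difference, but the error rate and sample size are worked out for one. What follows depends on how the primaries are to be read together.

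- **Any one positive supports the programme.** The overall false-positive rate exceeds the .05 in the power paragraph.
- **All three must be positive.** The error rate is protected, but the chance of success is well below what a one-test calculation gives.

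Under neither reading do the stated level and the stated sample size both fit the primary set. If the reading stays open until the results are known, the claim can follow whichever outcome turned out positive.

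**Working it through.** **Inputs from the article:** 3 primary outcomes; two-sided alpha .05; standardized effect d = 0.80; 3 covariates explaining R² = 0.10; 46 evaluable; 56 recruited 1:1; 20% attrition.

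**Assumptions, not in the article:** power of about 80% (inferred in step 1); the same d = 0.80 on all three outcomes; a common correlation r between the three test statistics, examined from 0 to 0.9.

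**Step 1. Reproduce the 46.** The normal-approximation total is N = 4(1 − R²)(z₀.₉₇₅ + z_power)² / d². At 80% power this is 4 × 0.90 × (1.960 + 0.842)² / 0.64 = 44.1, which is 23 per arm after rounding up, or 46. The same formula gives 40 at 75% power, 52 at 85% and 60 at 90%. So 80% is the usual level that returns 46, for one test at .05.

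Check with the noncentral t: noncentrality 0.80 × √(46/4) / √0.90 = 2.86, with 46 − 2 − 3 = 41 degrees of freedom. Power is 79.7%. The 46 therefore contains no allowance for more than one primary.

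**Step 2. Any one positive, each tested at .05.** Under independence, the chance of at least one false positive is 1 − 0.95³ = 0.1426. With correlation it is the probability that at least one of three equicorrelated standard normal statistics exceeds 1.96 in absolute value.

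**Step 3. All three must be positive.** With 80% power for each outcome, joint power under independence is 0.80³ = 0.512. With correlation it is the corresponding trivariate normal probability.

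| Assumed correlation | At least one false positive | Joint power, all three |
|---|---|---|
| 0 | 14.3% | 51% |
| 0.5 | 12.5% | 61% |
| 0.7 | 10.9% | 66% |
| 0.9 | 8.4% | 72% |

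**Step 4. Power per outcome with family-wise control.** Bonferroni and the first Holm step both use .05/3 = .0167. With N = 46 and the same noncentrality of 2.86, power is 64.3% by the noncentral t (67.9% by the normal approximation). Holm rejects whatever Bonferroni rejects, so 64% is a floor for each outcome under these assumptions.

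**Step 5. Sensitivity to the number analysed.** With 20% attrition, 56 × 0.80 = 44.8, about 45. By the noncentral t, the power of a single test is then 78.8%, first-step power 63.0%, and joint power 49% (r = 0) to 71% (r = 0.9). If all 56 completed, these would be 87.2%, 74.9%, and 66% to 81%. Full completion is no longer possible: the Results section reports 6 drop-outs among 36 enrolled (6/36 = 16.7%).

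**The case against.** **Multiplicity rules often sit in the analysis plan.** This is a condensed article, and the absence of such a rule is not in itself an error. That stands. What remains is what the article does fix: three co-equal primaries beside a sample size for one test. A later rule could settle the error rate, but controlling error across three unranked primaries, or requiring all three, changes the power behind the 46.

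**Testing each outcome at .05 is inferred.** The level appears only in the sample-size sentence, and no model is assigned to each primary by name. This also stands. Testing each at .05 is the plain reading, because no other level is given, but it is not stated outright.

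**The hypothesis might be taken as a stated joint success rule.** A reader might infer this because the Methods section joins the three domains with 'and'. The text does not support it. The sentence is a postulate about direction, and gaze control could also cover gaze performance, a secondary outcome. So the article cannot be said to be underpowered for a joint claim that it makes; it leaves the reading open.

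**The two harms are alternatives.** If all three must succeed, there is no inflation of error. And an error rate of nearly three times nominal holds only near independence; at r = 0.7 the ratio is 10.9/5, about 2.2.

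**It is a pilot.** The article says so more than once, which lowers the urgency. But it also states an objective of comparing therapeutic effectiveness, a superiority hypothesis and a formal sample-size calculation, so the mismatch still matters.

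**Conclusion.** The point holds as a mismatch between the set of primary outcomes and the one-test power paragraph. On the plain reading of .05 per outcome, the chance of at least one false positive is 14.3% under independence and 8.4% at a correlation of 0.9. If all three must be positive, joint power is about 51% to 72% over that range. The figures rest on an inferred power of about 80% and on assumed correlations; the joint power also needs d = 0.80 on every outcome, and would be lower if that value belongs to only one of them and the others are smaller.

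Severity: should be fixed. The pilot label tempers it, and the effectiveness comparison keeps it relevant.

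**What to change.** Before any between-group analysis, state that the three primary outcomes are tested with Holm's procedure at family-wise two-sided .05. Report unadjusted estimates and confidence intervals for all three. Restate the power paragraph to match: about 64% per outcome at the first Holm step with 46 analysed, d = 0.80, R² = 0.10 and 3 covariates.

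If the sponsor intends that all three must succeed, say so, keep .05 for each, and state the joint power with its assumed correlation.

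The cost is wording and a clearly lower stated power, from about 80% to about 64% per outcome at the first step. No new data or patients are needed.

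Naming a single primary outcome is not the preferred route. With 36 participants already enrolled it would change the endpoint mid-trial. Nor would it simply preserve the existing calculation: the .80 would first have to be shown to belong to the chosen outcome. Timing should be tied to the first between-group analysis, because the article describes blinding only of the assessors.
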